## Abstract

**Introduction:**

Lay health workers, despite their lack of formal trainings, are important partners in providing accessible care to people with risk to develop diabetes in the community. While pre-diabetes and diabetes are more prevalent among people with low socio-economic status, including those living in inadequate houses. However, this population often have accessibility problems to formal care services due to their financial and social disadvantages. In a high-income, developed Chinese society, this pragmatic randomized controlled trial seeks to investigate the effect of a 6-months lay health worker intervention in diabetes management among people living in sub-divided flats units in Hong Kong.

**Methods and analysis:**

In this trial, 222 Chinese primary caregivers living in inadequate houses and with diabetes risk will be recruited *via* non-profit organizations serving in districts with low average household incomes and prevalent subdivided flats in Hong Kong. Adopting a 6 months wait-list control, participants will be randomized to receive a 6-months lay health worker intervention of 5 components, including (1) lay health worker training and support; (2) health professional training; (3) formulation of a targeted care plan for the health and nutritional needs of the families; (4) case management approach; and (5) financial subsidy for lay health workers to sustain the practice. The control group will receive usual care and health information on diabetes risk management. Glycated hemoglobin (HbA1c) and fasting blood glucose will be taken at the entry and exit assessment of this trial as primary outcomes.

**Discussion:**

Our randomized controlled trial is one of the first to investigate the effect of lay health worker intervention on pre-diabetes management in a low-income Chinese population residing in inadequate houses. This study could provide insights to consider alternative service provision models to people living with diabetes risk in the community, by providing a care option to be supported by community health workers and enhanced community participation of care providers. This study attempts to evaluate the impact of a lay health worker intervention using a mixed-method study design. Despite its contribution, this study might be subjected to sampling bias since all the participants will be recruited from non-profit organizations serving deprived populations.

**Trial registration number:**

ChiCTR2100052080 in Chinese Clinical Trial Registry. URL: https://www.chictr.org.cn/edit.aspx?pid=134928&htm=4.

## Introduction

Diabetes is a major cause of preventable deaths globally. In 2019, diabetes affected 463 million populations and caused 1.5 million extra deaths directly (1). The developed, high-income countries have the highest prevalence, with 10% of the population is diagnosed with diabetes (2). Pre-diabetes and diabetes (including impaired fasting glycemia and impaired glucose tolerance, IGT), can be diagnosed by glycated hemoglobin (HbA1C) or 2-h plasma glucose based on 75-gram oral glucose tolerance test (OGTT). Without proper intervention, people with diabetes might be complicated from blindness, kidney failure, heart attacks, stroke, and lower limb amputation, which collectively contributes to 4.2 million deaths globally (2). Given the global cost of pre-diabetes and diabetes, early interventions and cost-effective disease management strategies offer an opportunity to reduce preventable disabilities and all-cause mortality in the general population.

Among all populations, people with lower socio-economic status are more prone to be identified with pre-diabetes/diabetes especially in developed economies. Socio-economic status is a multidimensional concept generally refers to the individual's income level, employment status, and educational attainment (3, 4). In the United States, the prevalence of diabetes was inversely related to household poverty level, which the group in the lowest federal poverty level has twice the odds of having diabetes compared to those ranked the highest (5). It can be explained by the findings of a meta-analysis, which indicates that low income, low educational level and low occupation were associated with a 40, 45, and 31% increased risk of developing type 2 diabetes in high-income countries (6). Similarly, in developed countries, pre-diabetes is more prevalent in the population with lower socio-economic conditions (7). On the other hand, low socio-economic status also impairs the management of diabetes. There is considerable evidence that low socio-economic status increases the risk of diabetes-related complications (8) and mortality (9).

Poor socio-economic status could limit individuals' choices of the living environment, and eventually lead to residing in inadequate houses. According to the United Nations, inadequate housing is a residence which fails any of the following criteria: (1) security of tenure; (2) availability of services, materials, facilities and infrastructure; (3) affordability; (4) habitability; (5) accessibility, (6) location, or (7) cultural adequacy (10). Deprived households might not be able to afford whole-flat residences, and eventually live in sub-divided flats. In Hong Kong, a developed high-income region in China, there are 0.2 million population residing in sub-divided flats in Hong Kong in 2016 (11). A survey revealed that more than 90% of the sub-divided flats households failed to meet at least one criterion of adequate housing, while half of the respondents did not have an independent kitchen and suffer from pest problems (12, 13). Sharing the challenge of worsening inequities with other Asian developed cities, Hong Kong have a Gini co-efficient of 0.54 in 2016, and its average flat price has rocket-raised to the top globally, indicating a worsening income inequality and difficulties in home ownership of the citizen (11). Against the backdrop of its extreme income disparity and growth of SDU resident size, Hong Kong could be an example of a high-income, developed city to investigate the health needs of people in inadequate environments in Asia.

Lay health workers are important partners in managing chronic disease including diabetes, through performing tasks related to health care delivery, despite their lack of formal professional trainings (14). Their responsibilities include facilitating the adoption of healthy practices, promoting access to care, supporting primary and chronic care, and advocating structural changes to cater to the health needs of a community (15). Lay health workers are particularly suitable for delivering support to hard-to-reach populations at a relatively low cost. Residing in the same community, lay health workers have shared backgrounds and connections with the people they are serving and therefore could provide assistance that is more culturally-sensitive and appropriate (14, 16). A randomized control trial has resulted in a reduction in HbA1c levels, body mass index and waist circumference of diabetic patients in 12 months. The diabetic patients in the intervention group have received three courses delivered by trained lay health workers with diabetes every 3 months, while the control group has received usual care (17). Another randomized control trial with a lay health worker intervention has also significantly reduced the HbA1c levels in diabetic patients. Patients were assigned to a control group with usual care, and an intervention group with trained lay health workers working with a registered nurse. Over the 12 months, the lay health workers have provided continuous support to the patients by conducting health education sessions, solving problems in diabetic self-management, mobilizing family support, and reinforcing adherence to medical appointment and medication regimens. Meanwhile, the nurse arranged meeting with patients, provided feedback to the physicians and supervised the work of the lay health workers (18).

However, there are inconclusive conclusion of the intervention effectiveness and further study is needed. There were three systematic reviews conducted on the effectiveness of lay health worker interventions on diabetes management (19–21). Authors note that there was high variability in study designs, diseases outcomes and measurements, leading to high risk of bias in the current studies (19–21). Also, some studies on lay health intervention of diabetes management did not clearly differentiate the intervention for people with type 1 and type 2 diabetes, and did not mention details of trainings provided to the lay health workers. There were also a wide range of duties covered by lay health worker in these studies, including language interpretation, conducting educational sessions, and providing health assessment (19–21). There was a high heterogeneity in content, duration, frequency and intensity of existing lay health worker intervention in literature and a robustly designed evaluation is needed to draw conclusion on its effectiveness.

This is a pragmatic, wait-list randomized controlled trial to evaluate the impact of lay health worker intervention on the incidence and disease management of pre-diabetes among people living in inadequate households. We hypotheses that the lay health worker intervention could significantly improve disease prognosis of people with a risk to develop diabetes, who are living in inadequate housing using an example of Hong Kong Chinese population.

## Methods and analysis

### Study design

This randomized controlled trial aims to evaluate the impact of a lay-health worker intervention on the disease management of type II diabetes mellitus (T2DM) among Chinese sub-divided flat residents units in Hong Kong, comparing to the wait-list controls who receive usual care. This trial is a part of a community, diabetes-screening programme which targets families living in sub-divided homes, aiming to provide disease management to the population diagnosed with diabetes or identified with risk to develop diabetes. This lay worker intervention contains five features, including: (1) lay health worker training and support; (2) health professional training, (3) formulation of a targeted care plan for the health and nutritional needs of the families; (4) case management approach; and (5) financial subsidy for lay health workers to sustain the practice. This trial will be reported in accordance with SPIRIT 2013 checklist (22), as enclosed in Supplementary material S1. Figure 1 comprises the workflow of this trial. Table 1 includes the minimal data set for trial registration.

**Figure 1 F1:**
[figure not shown]
CONSORT workflow of this trial.

**Table 1 T1:** Minimal data set for trial registration.

**Data category**	**Information**
Primary registry and trial identifying number	Chinese clinical trial registry ChiCTR2100052080
Date of registration in primary registry	16-Oct-21
Secondary identifying numbers	N/A
Source (s) of monetary or material support	The Hong Kong jockey club charities trust
Primary sponsor	The Hong Kong jockey club charities trust
Secondary sponsor (s)	N/A
Contact for public queries	[name] DFPH Jockey club school of public health and primary care, The Chinese University of Hong Kong, China
Contact for scientific queries	[name] DFPH Jockey club school of public health and primary care, The Chinese University of Hong Kong, China
Public title	Lay health worker as an example of medical task-shifting: design of a pragmatic randomized controlled trial for diabetes prevention in people living in inadequate housing
Scientific title	Lay health worker intervention on diabetes management
Countries of recruitment	Hong Kong, China
Health condition (s) or problem (s) studied	Diabetes
Intervention (s)	Active comparator: lay health worker intervention
	Placebo comparator: usual care with diabetes control information
Key inclusion and exclusion criteria	Ages eligible for study: ≥ 18 years and < 65 years
	Sexes eligible for study: both
	Accepts healthy volunteers: no
	Inclusion criteria: adult patient (≥ 18 years and < 65 years) who is the major caregiver of households living in sub-divided flat units in Hong Kong
	Exclusion criteria: mentally incapable to give consent
Study type	Interventional
	Allocation: randomized intervention model
	Parallel assignment
	Wait-list control of 6 months waiting period
	Primary purpose: prevention
	Phase I
Date of first enrolment	Nov-21
Target sample size	222
Recruitment status	Recruiting
Primary outcome (s)	Glycated hemoglobin (HbA1c)
Key secondary outcomes	Body mass index; Waist circumference; Percentage body fat; 3-day food records; Depression, anxiety and stress as measured by DASS-21; Quality of life as measured by ED-5D-5L

We will recruit participants from four NPOs in the Kwai Tsing, and Kowloon City districts in Hong Kong to participate in this study. In Hong Kong, social care services are delivered by NPOs and a list of NPOs subverted by public funding was publicly accessible at the Social Welfare Department, which multiple NPOs are responsible for the service delivery in each district. In this study, we do field investigation in the initial design stage of this protocol, and identify NPOs that are responsible for low-income family's services in the districts. The initial communication was established between the research team and the NPOs, of which four of them have agreed to be our recruitment sites for this project.

### Recruitment and training of lay health workers

Lay health workers will be recruited from retired population, local tertiary education institutes, and from the local community through collaboration with NGOs. Potential lay health worker who are (1) either fluent in Cantonese, Mandarin or English; (2) accomplish an education of secondary form 3 or above; and (3) committee to attend training session will be invited to an interview. There will be no restriction of age and sex of the lay health worker to be participated in this study. Upon recruitment, every lay health worker will need to go through a 10-h training session, which consists of the knowledge of conducting health assessment, motivational interviewing, and referral to formal support if necessary. The detailed training content and time distribution is presented in Supplementary materials S3 and S4.

Training will be conducted in the way of interactive training workshops given by a nurse, a dietitian, and public health practitioners to provide the introduction of medication management, nutritional knowledge, and health promotion skills. In the training session, the lay health workers will be given a set of training manuals and resources to guide their involvement in the programme. The training manual will be developed with reference to the evidence from the literature review for other volunteer-based training programmes, such as the Get Healthy Information and Coaching Service provided by the New South Wales Government of Australia (26). The training manual will include roles and responsibilities clarification, training in communication skills, needs assessment skills, trust-building advice, health and safety in a home setting, coping strategies for handling unexpected events, and skills to conduct motivational interviewing. Additional resources such as the instruments to be adopted in needs assessment and continuous monitoring of the health of the families, the detailed workflow of carrying the assessments, knowledge on providing basic consultation and identifying life-threatening symptoms, and skills for infection control during the pandemic will be provided. Furthermore, stimulations on the health need assessment, reinforcing behavioral change, and health monitoring will be done in the workshops. This training workshop will be a co-creation of the dietitian, nurse, social worker and public health practitioner in our inter-disciplinary team, which will create and synergies and knowledge transfer of professional knowledge across dietetics, nursing, public health science and social care.

To ensure the quality of training, all the workshops are conducted in an interactive manner and all the lay health workers must achieve a passing grade in the phone practicum and participate in the debriefing. Each workshop has multiple discussion sessions and quizzes to answer questions and provide opportunities for practice. The quiz is in the form of multiple-choice questions, and instructor will discuss the answers with the lay health worker immediately. The main purpose of the quizzes is to ensure the lay health workers understand the main concept of training, and facilitate in-class discussion with the instructors. All answers could be found in the training materials provided.

### Recruitment and training of healthcare professionals

Trainings will be provided to the healthcare professional to facilitate collaboration with the lay health workers. The primary care workers for the participants in community settings, including nurse and dietitians, will be invited to participate a 1.5-h interactive workshops and training in supporting them to familiarize with the role and strengths of the lay health workers. The interactive workshop will be given to them by the dietitian service lead and the nursing service lead in our project team, covering the project introduction, the overview of the service flow and the collaboration model with the lay health workers, and go through the administrative documents that would be used in the service. The health professionals will also receive a protocol to brief them on the rationales and operational details of this trial, and illustrate the clinical workflow of a lay-health worker intervention with real-case scenarios. Since the lay health workers will be responsible for a 6-month follow-up of the participants, the health professionals will learn how to hand over the case properly to the lay health workers. Moreover, the health professionals should expect to receive referrals for further investigation from the lay health workers when any red-flag symptoms or indicators of care plan occurred. During the face-to-face training session, healthcare workers will have a chance to meet their corresponding lay health workers to build rapport and trust in the working relationship, and therefore to facilitate the necessary referral that might happen during the intervention.

Each healthcare profession will be offered a shadowing session to shadow and observe a real-case practice with lay health worker as demonstrated by our project leads. Then, professional staff trainees will participate in a real-case trial session to conduct the intervention themselves with the LHW, and receive spontaneous feedback from our clinical service leads to ensure homogeneity of the service given. The clinical leads in our project team will review the case notes and collect feedbacks from the professional staffs engaging in the intervention regularly to audit the service quality. In both LHW and professional trainings, repeated rounds of real-case practices will be provided if the intervention quality is deemed as unsatisfactory.

### Lay health worker intervention content

A tailored behavioral change plan will be co-formulated by the lay health workers and the healthcare professional to cater the health needs of the participants. Upon the collection of consent, a needs assessment will be conducted to understand the health and nutritional needs of the participants in the community settings. Then, the primary care workers (who is a nurse or dietitian in this trial) will provide a face-to-face initial consultation session with the trial participants, and identify tailored health goals corresponding to the needs of the participants. Toward the end of the initial consultation, nurse/dietitian will introduce lay health workers to the participants, provide necessary information to ensure smooth handover and handling, and facilitate the rapport building between lay health workers and the participants. Then, the lay health workers will formulate a tailored behavioral change plan according to the health goals set, discuss the feasibility and readiness of the plan with participants, and be responsible for the monitoring of the behavioral change, and managing the self-reported health status of the participants since then through telephone consultation, once 2–4-week for 6 months.

This interventional will adopt a case-management approach. Upon the commencement of the tailored behavioral change plan, lay health workers will perform behavioral change monitoring through the 6-months period, under the supervision of the nurse/dietitian. The lay health workers will adopt a case-management approach, which each participant will be follow-up by the same lay health workers throughout the intervention, to allow the change monitoring to be done based on a trusted relationship. Each of the lay health workers will not be managing more than four families in the same period. To better facilitate behavioral change, the lay health workers will adopt the Stages-of-Change Model, which was developed by James Prochaska and Carlo DiClemente in 1983 (27). The model describes personal behavioral change in five stages, namely pre-contemplation, contemplation, preparation, action, maintenance, and relapse. Stage-of-Change Model is widely adopted in health psychology field and behavioral interventions (28, 29). In our proposed intervention, lay health workers will assess which stage the client is in, and motivate the client to move on to the next stage until the maintenance stage (27). During each follow-up, the lay health workers will review pre-established health goals with the participants, identify the facilitators and barriers of the participants' behavioral changes, and provide recommendations for the participants to overcome the identified barriers through motivational interviewing. Motivational interviewing is a “collaborative, goal-oriented style of communication with particular attention to the language of change,” with the aim to strengthen the person's motivation and commitment for the health behavior goal in an accepting and compassionate atmosphere (30).

Alongside the case management duties, lay health workers will continuously assess the physical, mental, and nutritional health status of the participants through patient-reported outcomes. Lay health workers will maintain a close working relationship with the nurse and dietitian. Following each of the telephone follow-up, the lay health workers will participate in a group-based case de-briefing session where they can discuss the difficulties they encountered during the follow-up, and learn from each other's for better consultation skills. Lay health worker will review case progress with nurse/dietitian once every 2–4 weeks, and will discuss the motivators and barriers for the participants' behavioral changes to guide necessary amendments in the care plan. The participants are, therefore, under the co-management of the clinical professional (nurse or dietitian) and the lay health workers. For there is any undesirable outcome identified during the follow-up, the lay health workers will refer the participants for immediate intervention by the nurse and dietitians' management.

Lastly, financial subsidy will be provided to lay health workers to ensure the sustainability of their practice, and as a reward to honor their time spent on providing services to the participants.

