### Sample size calculation

Two hundred and twenty-two participants are needed (111 for intervention, 111 for control at a 1:1 case to control ratio) to attain 80% power, 95% level of significance and 20% dropout rate in a population with an expected population standard deviation of 1.5, and an allowable difference of 0.01 to detect a change of 0.5% change in HbA1c concentration. We plan to train 70 lay health workers on a 1:4 lay health worker to patient ratio, and assuming a 20% dropout rate.

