In order to compare the effectiveness of intervention between control and the intervention group at the exit assessment of intervention (6^th^ month), we will use repeated-measures Analysis of Variance (ANOVA) for parametric outcomes. We will consider the measures of data at baseline (0^th^ month) and covariates that are imbalanced in control and intervention groups when conducting ANOVA, and the effect size will be estimated by calculating the Cohen's *d* value. For non-parametric variables, the Friedman test will be done, and Kendall's W value will be produced for effect size estimation. For ordinal data, we will use Generalized Estimating Equations to compare groups at each follow-up (0^th^ month, 6^th^ month, and 12^th^ month), allocation group (intervention and wait-list control), time by group interaction, covariates that are imbalance between groups, and important socio-economic variables including sex, age, and education level. We will use an identify link function given a normal distribution of the captioned outcome. Also, Kaplan-Meier curves will be drawn to capture the comparison of diabetes-free survival in the intervention and control group. The level of significance is set at 5% m and *post-hoc* adjustment will be applied for multiple comparisons. Multiple imputations will be used whenever appropriate for missing data. In this analysis, all statistical analyses will be conducted using R and RStudio, and the Cohen's *d* value will be estimated using G^*^Power.

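### The analyses named for month 6 have no lay health worker term, so if outcomes correlate within worker the standard error is modestly too small

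*Protocol article*

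**What the plan says.** Participants are randomised individually (Randomization and binding), and only one member of a household can enrol (Selection of subjects), so a family counts as one participant.

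Under Lay health worker intervention content, "each participant will be follow-up by the same lay health workers throughout the intervention", and "Each of the lay health workers will not be managing more than four families in the same period". The worker draws up the behavioural plan, makes the calls every two to four weeks and does the motivational interviewing. Under Control group selection, controls have usual care for six months and meet the lay health workers only afterwards.

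On numbers, Sample size calculation states "Two hundred and twenty-two participants are needed (111 for intervention, 111 for control at a 1:1 case to control ratio", and in the same paragraph "We plan to train 70 lay health workers on a 1:4 lay health worker to patient ratio", with 20% dropout assumed. It mentions no ICC or design effect.

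On analysis, the Data analysis section says that for the comparison at month 6 "we will use repeated-measures Analysis of Variance (ANOVA) for parametric outcomes". The terms it adds are the baseline value and imbalanced covariates. Non-parametric outcomes get a Friedman test. Ordinal outcomes get GEE with time, group, their interaction, imbalanced covariates, sex, age and education. No model has a worker term or a variance clustered by worker.

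**The concern.** Participants coached by the same person may end up more alike than participants coached by different people. The protocol builds in that possibility by keeping each participant with the same worker throughout. At month 6 the data are partially nested: small clusters in the intervention arm, single individuals in the control arm. The between-participant error term of the named ANOVA treats everyone as independent. If there is within-worker correlation, confidence intervals for the primary comparison are somewhat too narrow and p-values somewhat too small. The protocol presents lay health workers as a model of care, so variation between workers is also of interest in itself.

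**Working it through.** **Inputs.** Sample size calculation: 111 per arm, 70 workers trained, 1:4 ratio, 20% dropout. Lay health worker intervention content: cap of four families. Data analysis: significance level 5%, taken here as two-sided because sidedness is not stated. Assumed, because the protocol gives none: ICC of 0.05 and 0.10 for the quantity tested (the change, or the baseline-adjusted month-6 value).

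**The plan's worker number.** 222/4 = 55.5 and 55.5/0.8 = 69.4, which rounds up to the stated 70. So 70 workers is enough for four participants each across both arms after dropout.

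**Caseload during the month-6 comparison.** Retained workers: 70 × 0.8 = 56. Only the 111 intervention participants have a worker in this period.
- If all 56 serve in the first slot: 111/56 = 1.98, about 2 each.
- If each worker serves one slot only: 56/2 = 28 and 111/28 = 3.96, about 4 each, which is the cap.

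The protocol does not say which deployment applies.

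**Formulas.** With *m* participants per worker in one arm, 1:1 allocation and equal total variance in the arms:
- design effect in the intervention arm: DE = 1 + (*m* − 1) × ICC
- variance of the difference relative to independence: V = (1 + DE)/2
- shortfall of the naive standard error: 1 − 1/√V
- true type I error: 2 × [1 − Φ(1.96/√V)]

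Example, *m* = 4 and ICC 0.10: DE = 1.30, V = 1.15, √V = 1.072, 1.96/1.072 = 1.828, type I error 6.8%.

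| *m* | ICC | V | SE too small by | Type I error | N for the precision planned at 222 (222 × V) |
|---|---|---|---|---|---|
| 2 | 0.05 | 1.025 | 1.2% | 5.3% | 228 |
| 2 | 0.10 | 1.05 | 2.4% | 5.6% | 234 |
| 4 | 0.05 | 1.075 | 3.6% | 5.9% | 239 |
| 4 | 0.10 | 1.15 | 6.7% | 6.8% | 256 |

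Coverage of a nominal 95% interval is 100% minus the type I error: 94.7% and 94.4% for two per worker, 94.1% and 93.2% for four. A simulation of t tests on clustered data (40,000 runs per setting) gave 5.8% to 6.0% for *m* = 4 and ICC 0.05, in line with the formula.

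**After dropout.** With 111 × 0.8 = 88.8 completers over 56 workers, the load is about 1.6 and the type I error 5.2% to 5.3% for the same ICCs. Four enrolled per worker becomes 3.2 on average, so four is an upper bound here too.

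**Power.** With SD 1.5, difference 0.5 and 111 per arm, two-sided power is 70% under independence. A correct analysis has 69% to 68% with two per worker and 67% to 64% with four. The distance from 80% to 70% comes from the sample size calculation, not from clustering, and is a separate matter.

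**The case against.** **No ICC is documented.** At an ICC of zero nothing changes. The mechanism is the worker's coaching: if coaching affected nobody, it would create no variance between workers, and the type I error would stay at 5%. Inflation needs coaching that differs between workers yet averages to no effect. The protocol also limits worker differences: a nurse or dietitian sets the health goals, a phone practicum must be passed, practice is repeated if unsatisfactory, and workers are supervised and debriefed in groups. This stands as far as the point must be conditional. It does not remove it, because interval coverage suffers whenever coaching effects differ between workers, whatever their average.

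**Four per worker is a cap.** This stands. About two each is equally compatible with the text, and the effect is then very small.

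**A condensed article may leave this to an analysis plan.** This stands only in part. The article fixes the models, lists their terms and sets the sample size next to the 1:4 ratio, all without worker. Followed as written, it gives the naive standard error.

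**Stronger readings.** A reader might infer that the result would generalise only to the workers used. With 28 to 56 workers and small caseloads, the figures above do not support that. A reader might also infer a fall in power from 60% to 55% by combining 89 completers per arm with four analysed participants per worker. That keeps the full caseload after dropout, and the 60% start reflects the separate sample size problem. Unequal variances between arms add little at 1:1 allocation.

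**Conclusion.** The point holds in a conditional and modest form. The protocol groups intervention participants by worker, leaves controls ungrouped until after month 6, and names analyses without a worker effect. For any positive within-worker correlation the month-6 standard error is too small. Over assumed ICCs of 0.05 to 0.10, it is too small by 1.2% to 2.4% at two participants per worker and by 3.6% to 6.7% at four. The type I error is 5.3% to 5.6% and 5.9% to 6.8% respectively.

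These figures rest on the assumed ICCs, equal caseloads, equal total variance in the arms and a two-sided 5% test. A reader might conclude that the standard errors are definitely wrong, or that the four-per-worker figures are the expected case. The documents support neither, because they give no ICC and no caseload per period. Shared nurses, dietitians and debriefing groups could form larger clusters, but their numbers are not stated and no size can be put on this.

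**What to change.** - Record the lay health worker's identifier for each participant. Table 2 already counts families followed by the same worker from administrative data, so the link should exist.
- Allow for worker in the month-6 comparison in one of two ways, chosen in advance: a partially nested mixed model (random worker effect in the intervention arm only, with small-sample degrees of freedom), or cluster-robust standard errors with each control as its own cluster. With two to four participants per worker the random-effect variance may be estimated near zero, so the robust option is a full alternative.
- Report the ICC with its interval, and state whether workers serve one slot or both.
- For any month-12 group comparison, such as the GEE, cluster by worker in both arms, because controls will by then have been offered a worker.

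This changes nothing in recruitment, treatment or visits. The cost is one identifier, a different model call, slightly wider confidence intervals and an imprecise worker variance. Whether to replace the repeated-measures ANOVA by a baseline-adjusted model is a separate question.
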